### Sample size

We estimated that the control group will have a cumulative 3-year diabetes incidence rate of 25 %. This estimate lies between a lower rate (19 %) found in a trial involving women considerably leaner [9] and higher rates found in two trials: a trial of a very high risk postpartum group (36 %) [8] and another trial involving older women, enrolled a decade after their first pregnancy with GDM (38 %) [4]. We also assume that the intervention will produce a reduction of 40 % in diabetes incidence over three years. This estimated effect is lower than the incidence reduction observed in the DPP subgroup analysis (53 %), consistent with our anticipated intervention’s effect, and clinically meaningful for the prevention of diabetes in Brazil. The number needed to treat to prevent one case of diabetes is 10 (1/(.25-.15). Under an exponential model, the relative risk of 0.60 comparing intervention to control corresponds to a hazard ratio of 0.565.

We based our sample size calculation on a Cox proportional hazards model test of a one-sided primary hypothesis (no difference between treatments in incidence of type 2 diabetes) at the 0.025 level, with 90 % power, using the package RCTdesign in the software R, version 2.14. Utilizing a group sequential design, we plan for four analyses, three interim and one final with symmetric O’Brien-Fleming boundaries for efficacy and futility to be spaced evenly in information time. This analysis shows that 135 observed events in both arms are needed at the time of final analysis to have 90 % power to detect a true hazard ratio of 0.565. Assuming an annual drop-out rate of 5 %, an average monthly recruitment of 18 participants, and requiring an average follow-up time of three years if the study continues to the final analysis, we calculated a total sample size of 740 for the trial.

To enroll this number of women, we estimate that up to 7400 women will have to be initially screened. If we are unable to maintain our monthly recruitment goals with the strategy outlined above, we will consider other means of recruitment.

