### Ethical issues

The trial protocol was approved by the ethics committee of the Hospital de Clínicas de Porto Alegre (Project 120097, May 4, 2012). Written consent is obtained at initial recruitment and then again, before enrollment to the trial. At randomization we explain to the participants that they will have equal chances of being entered into one or the other group. We also explain that it is not known whether applying a more intense intervention relatively soon after postpartum is more beneficial than the conventional approach. However, if the Study finds that it is indeed more beneficial, then at study close-out those who did not receive the more intense approach will be informed about how to undertake the activities found to be successful. While we emphasize the importance of maintaining participation throughout the study so as to minimize bias in the trial results, women are informed that they may request to terminate participation if they so decide. Those who drop out of the study will nevertheless have their available follow-up time included in analysis of treatment effects. Women found to have developed diabetes will be notified and oriented to seek medical attention to confirm diagnosis and initiate treatment.

A data and safety monitoring board (DSMB) will monitor efficacy (or futility) and adverse effects. Based on these considerations, the DSMB may recommend that the protocol be modified or that the LINDA trial be terminated. The DSMB will consist of experts in relevant biomedical fields, biostatistics and medical ethics.

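### The 135 events and the 0.025 level match a binding futility boundary, yet stopping is only a DSMB recommendation; overriding futility lifts the one-sided error to at most 0.0263, with no loss of power

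*Protocol article*

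**What the plan says.** All the design inputs are in the Sample size section of the protocol article. The test is a "Cox proportional hazards model test of a one-sided primary hypothesis", run "at the 0.025 level, with 90 % power, using the package RCTdesign in the software R, version 2.14". On monitoring, "we plan for four analyses, three interim and one final", with symmetric O'Brien-Fleming "boundaries for efficacy and futility to be spaced evenly in information time". The effect is derived in the same section: "the relative risk of 0.60 comparing intervention to control corresponds to a hazard ratio of 0.565". The result follows: "This analysis shows that 135 observed events in both arms are needed at the time of final analysis". Allocation is 1:1 (Randomization section).

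The Ethical issues section gives the DSMB the task of monitoring efficacy or futility as well as adverse effects, and says that on this basis "the DSMB may recommend that the protocol be modified or that the LINDA trial be terminated". The article prints no boundary values and does not say whether the futility boundary is binding.

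**The concern.** A futility boundary can be used in two ways when the efficacy boundary is calculated. If it is binding, a trial that crosses it must stop. Paths that would have dipped below futility and later recovered to a false positive are then removed, and the efficacy limits can be relaxed slightly while the level stays at 0.025. If it is non-binding, no such credit is taken.

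The printed event count turns out to identify the binding version. The efficacy limits therefore rest on a stop that the article leaves to a recommendation. If the trial continued after a futility crossing and ended with a marginally positive primary result, the stated 0.025 level would no longer hold exactly, and a critic could say so.

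**Working it through.** **Inputs.** One-sided level 0.025, power 0.90, hazard ratio 0.565, four looks at information fractions t = 0.25, 0.50, 0.75 and 1, and symmetric O'Brien-Fleming boundaries (Sample size); 1:1 allocation (Randomization). Assumption: the variance of the log hazard ratio is 4/d for d events. The hazard ratio checks: ln 0.85 / ln 0.75 = 0.5649.

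**Fixed-sample reference.** d = 4(1.960 + 1.282)² / (ln 0.565)² = 128.9 events.

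**Reproducing the 135.** Let S(t) be the score process with mean θt and variance t. Efficacy is S ≥ c. Symmetric futility is S ≤ 2ct − c, which meets efficacy at t = 1. On the Z scale the efficacy limit is c/√t and the futility limit is (2ct − c)/√t. Recursive numerical integration, with c solved for a level of 0.025 and futility binding, gives c = 2.003:

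| Look | Events | Efficacy Z | Futility Z | Efficacy HR | Futility HR |
|---|---|---|---|---|---|
| 1 | 33.75 | 4.006 | −2.003 | 0.252 | 1.99 |
| 2 | 67.5 | 2.833 | 0 | 0.502 | 1.00 |
| 3 | 101.25 | 2.313 | 1.157 | 0.631 | 0.795 |
| 4 | 135 | 2.003 | 2.003 | 0.708 | 0.708 |

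The drift for 90 % power is 3.3107, so d = 4 × 3.3107² / (ln 0.565)² = 134.5, rounded up to 135. This is the plan's figure.

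**Do other readings also give 135?**
- Efficacy-only O'Brien-Fleming: c = 2.024, 131.8 events (132).
- Non-binding futility, level held at 0.025: 135.97 events (136) with the futility limits above, or 136.15 (137) if the futility line is recomputed with c = 2.024.
- Binding, but with the futility line set by a type II error of 0.10: 138.8 events (139).

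Of these, only the binding symmetric design gives 135.

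**One-sided error with the planned efficacy limits when futility is overridden:**

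| Futility looks overridden | One-sided error |
|---|---|
| none | 0.0250 |
| look 1 only | 0.0250 |
| look 2 only | 0.0251 |
| look 3 only | 0.0261 |
| looks 2 and 3 | 0.0263 |
| all three | 0.0263 |

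The largest value is 0.02635, an excess of about 0.0013. A direct multivariate normal calculation gives the same 0.02635. A simulation of 40 million paths gives 0.0263 with futility ignored and 0.0250 with it obeyed.

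**Power at 135 events and hazard ratio 0.565:**

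| Efficacy limits | Futility obeyed | Futility ignored |
|---|---|---|
| planned (final Z 2.003) | 90.1 % | 91.0 % |
| without credit for futility (final Z 2.024) | 89.8 % | 90.7 % |

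**The case against.** The strongest case on the other side has four parts.

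- **The effect is very small.** The excess of 0.0013 is a worst case. Under no effect, the probability of crossing futility by look 3 is about 0.88, and 0.00135 / 0.88 means that roughly 1 in 650 such trials would later become a false positive if continued. The disputed zone at the final analysis is an observed hazard ratio between 0.706 and 0.708, where the nominal one-sided p-value is 0.0215 to 0.0226, still below 0.025. All of this stands and sets the priority.
- **The two sections do not contradict each other.** One plans futility boundaries and the other has a board monitor futility and advise. The wording on recommendations is general and also covers adverse effects and protocol changes. It does not declare futility non-binding, and nothing in the article says that the trial would continue after a crossing. This stands too: the point is conditional on an override that the article permits but does not plan.
- **Binding status belongs in an analysis plan or DSMB charter that is not shown.** This is fair as to the silence. The point rests instead on the printed 135, 0.025 and boundary family, which together identify the binding design, set beside an advisory board.
- **A binding design is a legitimate choice.** True, provided that a crossing does end the trial.

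A reader might infer that 135 events are too few unless futility is always obeyed. The numbers do not support this: overriding futility raises power, and 135 events give at least 90 % with either set of efficacy limits when futility is not acted on. A reader might also take the chance of crossing futility as the size of the problem. Under no effect it is 50 % by look 2 and 88 % by look 3. At a hazard ratio of about 0.77, implied by the 15 % v 19 % in the Chinese trial cited in the Background, it is 45 %. These are not false-positive rates, and at 0.77 the null hypothesis is false, so no type I error can occur.

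**Conclusion.** The concern holds in a limited form. The stated 135 events and 0.025 level match symmetric O'Brien-Fleming boundaries with binding futility, while the article makes stopping a recommendation. If every futility crossing were overridden, the one-sided error would be 0.0263 instead of 0.0250; overriding the third look alone gives 0.0261. The sample size is not in error and power is not at risk.

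This rests on three assumptions: evenly spaced looks as planned, the variance 4/d, and the reading of the symmetric design that reproduces 135. Under the variant with the futility line set by a type II error of 0.10, the error with futility ignored would be 0.0280, but that variant needs 139 events and does not fit the printed figure. The priority is low: a cheap gain in robustness.

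**What to change.** Before any interim look, state in the protocol and the DSMB charter that the futility boundary is non-binding, and compute the efficacy boundary without credit for it: Z = 2.0243/√t, that is 4.049, 2.863, 2.337 and 2.024, in place of 4.006, 2.833, 2.313 and 2.003. Keep the futility limits as guidance to the board. The alternative is to state that futility is binding and align the Ethical issues wording with that. Timing matters, because a choice made after a crossing would carry little weight.

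The cost is small. The final critical hazard ratio moves from 0.708 to 0.706. If futility is obeyed, power at 135 events is about 89.8 % instead of 90.1 %. Either restate that figure or plan for 136 events (137 if the futility line is recomputed with the new constant) to restore 90 %. No extra women are needed.

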### Ethical issues

The trial protocol was approved by the ethics committee of the Hospital de Clínicas de Porto Alegre (Project 120097, May 4, 2012). Written consent is obtained at initial recruitment and then again, before enrollment to the trial. At randomization we explain to the participants that they will have equal chances of being entered into one or the other group. We also explain that it is not known whether applying a more intense intervention relatively soon after postpartum is more beneficial than the conventional approach. However, if the Study finds that it is indeed more beneficial, then at study close-out those who did not receive the more intense approach will be informed about how to undertake the activities found to be successful. While we emphasize the importance of maintaining participation throughout the study so as to minimize bias in the trial results, women are informed that they may request to terminate participation if they so decide. Those who drop out of the study will nevertheless have their available follow-up time included in analysis of treatment effects. Women found to have developed diabetes will be notified and oriented to seek medical attention to confirm diagnosis and initiate treatment.

A data and safety monitoring board (DSMB) will monitor efficacy (or futility) and adverse effects. Based on these considerations, the DSMB may recommend that the protocol be modified or that the LINDA trial be terminated. The DSMB will consist of experts in relevant biomedical fields, biostatistics and medical ethics.

### Final considerations

After testing instruments and piloting strategies and procedures, we initiated trial recruitment and randomization in January, 2015.

## Discussion

To our knowledge, this is one of the few randomized trials designed to prevent diabetes by intervening shortly after delivery of women with GDM. As such, the experience gained with respect to the specific issues related to intervention during this special phase of women’s lives should add important knowledge to the field of diabetes prevention worldwide.
